**Figure 2 F2:**
[figure not shown]
Logo of the DAILY therapy study. The logo represents a clock in which the letters act as hands. The clock is set at a full hour, which should underline the desired regularity in everyday life. The color green is synonymous with life and health.

### Allocation

Participants are allocated to either the intervention or control group by a computer-generated randomization list. Each test person is assigned an individual study code, which contains information about the current ward and gender, and otherwise consists of a sequential number. Personal data that could reveal identity and participation in the intervention or control group are not part of the code. The decoding of the code is only allowed for study staff. Until the end of the study, the participants will not be informed about their assignment to the intervention or control group. However, after the end of the study, participants will be informed about their group affiliation and participants of the control group will be given the opportunity to learn about the circadian system and the importance of a structured daily routine.

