### Setting

DAILY is a single site study conducted at the specialist ward for addiction disorders and the outpatient clinic for substance use disorder of the Clinic for Psychiatry and Psychotherapy at the University Hospital of Munich. There are 24 patients with a minimum age of 18 years on the ward, with men and women admitted equally. The day clinic treats 15 patients with a minimum age of 18 years simultaneously. On the ward and in the day clinic there are fixed, individually determined schedules for therapy sessions from which patients are not allowed to deviate. Meals are offered by the clinic at fixed times of the day, but do not have to be taken. Patients are free to leave the ward and the day clinic between therapy sessions in order to take meals outside or to pursue other activities such as walks or sports. The ward is open in principle, but care is taken to ensure that patients do not leave it between 10 pm and 8 am. There are no fixed sleeping hours on the ward, except that patients must arrive on time for their therapy sessions, which usually start between 08:30 and 11:00 am. On the weekend, patients of the ward have no regular appointments. Patients of the Day Clinic leave the clinic in the afternoon and arrange the rest of the day and their weekends independently. In addition, food can be brought to the ward and the day clinic and snacks can be eaten at any time. Both clinics are interdisciplinary staffed by medical doctors, psychologists, nurses, and social workers, all of whom have broad experience in the treatment of substance use disorders, including AUD. About half of the patients on both sites are diagnosed with AUD, the other half suffers from multidrug dependency. On the ward a qualitative detoxification program with psychotherapeutic services is offered to AUD patients and patients with multidrug use. In the day clinic the same psychotherapeutic services are offered as on the ward, but the patients are already detoxified, and the therapy takes place on a day-care basis.

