### Standard Therapeutic Services on the Ward and the Day Clinic

In parallel to the DAILY or the sham treatment, all patients receive the standard clinical treatment consisting of medical and psychological consultation, individual and group therapy (combining Motivational Enhancement Therapy and Cognitive Behavioral Therapy), and medication if necessary. The psychotherapeutic treatment of AUD and multiple substance use patients is the same but is conducted separately. The standard psychotherapy concept of the ward and the day clinic includes motivation work in which the incentive to abstinence and the decision to change consumption behavior is increased. In addition, situation analyses, the identification of risk factors, and the development of alternative actions are used to work with patients on relapse prevention. In addition, all patients receive psychoeducational therapy sessions to provide theoretical knowledge about the definition of addiction and its development on a neurobiological level. The treatment of AUD patients on the ward is scheduled for 14 days. In the day clinic, the treatment time ranges from 2 to 4 weeks and the concepts described above are elaborated in more detail and sociotherapy is also offered. In none of these standard therapies the advantages of daytime structures and regular sleep times are discussed.

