### Study Population

Men and women, unemployed and employed subjects are equally included in the study. Depending on whether the subjects are patients of the ward or day clinic, they are in detoxification or post-detoxification treatment. Study enrollment of subjects who are newly admitted to the detoxification program of the ward will take place at the earliest after 5 days of detoxification, to exclude cognitive and physical limitations caused by acute intoxication and its after-effects. Study participants who are discharged from the ward either go home, receive further treatment in the day clinic, or go to other institutions for long-term therapy. Study participants who are discharged from the day clinic either go home after discharge or go to other institutions for further treatment. The health conditions of all test persons allow them to perform their daily tasks without external assistance. Approximately half of the study subjects have a regular job, while the others are unemployed or retired. Usually 3–5 subjects are involved in the study simultaneously.

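### The stated between-arm analysis ignores whether a patient was recruited on the ward or in the day clinic, and no stratification by setting is described

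*Protocol article*

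**What the plan says.** The Allocation section gives the method in one sentence: "Participants are allocated to either the intervention or control group by a computer-generated randomization list". It mentions no strata or blocks. Setting is known at that point, because each participant has a study code "which contains information about the current ward and gender".

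The two recruitment settings differ in stage of treatment. Under Study Population: "Depending on whether the subjects are patients of the ward or day clinic, they are in detoxification or post-detoxification treatment". Enrolment of newly admitted ward patients "will take place at the earliest after 5 days of detoxification", while in the day clinic "the patients are already detoxified, and the therapy takes place on a day-care basis" (Setting). Scheduled stays differ too: "The treatment of AUD patients on the ward is scheduled for 14 days" and "In the day clinic, the treatment time ranges from 2 to 4 weeks" (Standard Therapeutic Services).

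The Data Analysis section sets out the between-arm comparisons. Endpoint values are compared by unpaired tests (t-test, Mann-Whitney, Kruskal-Wallis and one-way ANOVA are the examples). Changes from start to end are compared by an analysis such as two-way ANOVA. The multiple regressions name four predictors: Routine Variability Scores, depression level, severity of alcohol consumption and self-efficacy. Neither setting nor detoxification stage is among them.

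**The concern.** By the article's own account, recruitment setting bears on the outcomes in three ways.

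- **Drinking.** The Timeline Followback looks back 30 days, so its baseline value depends on how long ago detoxification began.
- **Regularity.** Ward patients are kept in overnight, whereas day-clinic patients leave each afternoon and arrange their own weekends (Setting). The Limitations section says clinic routines already structure patients' days.
- **Circadian state.** The Background says withdrawal itself disturbs circadian rhythms, and ward recruits are closer to it.

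In a sample of a few dozen, the arms can differ noticeably in ward share by chance. An analysis without setting then carries that difference into several outcomes at once. It also leaves between-setting variation in the error term, even when the arms are balanced.

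**Working it through.** The article states no sample size, power or effect size, so there is no figure to reproduce. The steps below measure how large a chance imbalance could be and what it would do.

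**Inputs**
- *Sample size (assumed).* Study Population gives 3 to 5 participants at a time, each for 6 weeks, and Design gives one year of recruitment. 52/6 × 3 = 26 and 52/6 × 5 = 43.3, so N = 26, 34 and 44 are used.
- *Ward share (assumed).* Setting says: "There are 24 patients with a minimum age of 18 years on the ward". It gives 15 places for the day clinic. 24/39 = 62%, with a range of 50% to 75%.
- *Arms.* Equal size, simple randomisation (assumed).
- *Setting effect on an outcome (assumed).* 0.5, 0.8 or 1.0 within-setting SD.
- *Test.* α = 0.05, taken as two-sided.

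**Step 1: baseline look-back.** A patient enrolled after 5 days of detoxification has about 30 − 5 = 25 look-back days before admission. A day-clinic patient arriving directly from a 14-day ward stay has about 30 − 14 = 16. The second route is an assumption, since the article does not say how long before day-clinic entry detoxification took place. Baseline drinking scores therefore do not mean the same thing in the two settings.

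**Step 2: chance of imbalance.** With K ward patients among N and n = N/2 per arm, the ward count X in one arm is hypergeometric. The gap in ward share is |2X − K|/n. Example: for N = 26, K = 16, n = 13, a gap of at least 0.20 needs |X − 8| ≥ 1.3, so X ≤ 6 or X ≥ 10, with probability 0.226.

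| N | Ward share 50% | 62% | 75% |
|---|---|---|---|
| 26 | 0.434 | 0.226 | 0.160 |
| 34 | 0.169 | 0.157 | 0.225 |
| 44 | 0.131 | 0.215 | 0.162 |

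These are the probabilities of a gap of 20 points or more. They do not fall smoothly with N because only whole patients can be allocated. For gaps of 30 points or more the range is 3% to 23%. At N = 100 the 20-point probability is 2% to 7%.

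**Step 3: consequence under no treatment effect.** This used 40,000 simulated trials per combination, ward share 62%, and an unadjusted t-test.
- Over all trials, type I error is 0.049 to 0.051 and the mean estimate is essentially 0.
- A gap of 20 points or more in one given direction occurs in about 8% to 11% of trials.
- Within those trials the mean spurious difference is 0.13 SD (N = 44, effect 0.5 SD) to 0.34 SD (N = 26, effect 1.0 SD).
- Within those trials, false significance in the direction of the imbalance occurs in 5.5% to 11.4%, against 2.5% nominal.

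**Step 4: precision.** Leaving out a setting effect of d SD at ward share p multiplies the outcome variance by 1 + d²p(1 − p). With p = 24/39, p(1 − p) = 0.237. The factor is 1 + 0.25 × 0.237 = 1.06 for d = 0.5, and 1.24 for d = 1.0.

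**Step 5: with stratification.** Under permuted blocks of 4 within setting, the ward count can differ between arms by at most 2 patients: 2/13 = 15, 2/17 = 12 and 2/22 = 9 points for N = 26, 34 and 44.

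**The case against.** **Condensed article.** Strata, blocks and covariates are commonly left to the full protocol, which is not shown. The singular word for the list is compatible with a stratified list, and a study code carrying ward and gender is compatible with strata. This stands: a reader might infer that both settings are drawn from one unstratified list, but the text does not establish it. The tests are also introduced only as examples. The analysis part of the point survives, because the comparisons are written out and the predictor list is worded as complete and lacks setting.

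**Randomisation.** A reader might infer that natural recovery could systematically pass for a DAILY effect. That is not supported. Recovery happens in both arms, chance imbalance has no preferred direction, and Step 3 shows no overall bias or inflation of error.

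**Time in care.** A reader might also infer that recruitment setting fixes how much of the six weeks is spent in care. The article's own durations say otherwise. Someone enrolled on ward day 6 has 9 ward days left, so 42 − 9 = 33 study days after discharge if sent home, but 42 − 9 − 28 = 5 after a further four weeks of day clinic. A patient starting in the day clinic has 14 to 28. The wide contrast is between two ward recruits with different destinations. The Limitations section already says the analysis must take account of those who move to other clinics.

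**Choice of N.** At N = 20 and a 50:50 split the 20-point probability would be 66%, but that N lies below the accrual the article implies.

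**Pilot status.** The Design section says proof of treatment success is not the main focus. This lowers the stakes. The article nevertheless names efficacy outcomes as primary and tests them at 0.05.

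**Conclusion.** The point holds as a weakness in the stated analysis and an unreported feature of the allocation. It does not show a biased trial. Two stages of treatment are mixed, setting is recorded before allocation, and the between-arm analyses as written do not use it. Under the assumed N of 26 to 44 and ward share of 50% to 75%, a gap of 20 points or more has a chance of 13% to 43%. Conditional on such a gap, the assumed setting effects give a mean spurious difference of 0.13 to 0.34 SD at a 62% ward share. The loss of precision is small if the setting effect is near 0.5 SD and more noticeable near 1.0 SD. N, ward share and setting effect are not in the article, so these figures indicate scale only.

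**What to change.** **Analysis.** In the Data Analysis section, include recruitment setting together with the outcome's baseline value in every between-arm comparison. ANCOVA would serve for continuous outcomes. Where a rank method is needed, a setting-stratified rank test such as van Elteren's could be applied to the change from baseline. Baseline alone is not enough, given Step 1.

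**Allocation.** State whether the list is stratified by setting. If it is not, stratify the remaining allocations by ward versus day clinic with permuted blocks of varying size, concealed from the staff who recruit. Patients already allocated keep their assignment and are handled by the adjusted analysis.

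**Cost.** The analysis uses one or two model degrees of freedom, which offsets part of the gain if the setting effect is small. Setting is already in the study code, so no visits or patients are added. Blocks within small strata make allocation somewhat easier to guess. That matters here because study staff recruit participants and may decode the study code, so concealment has to be arranged deliberately.

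**What it leaves open.** Discharge destination arises after randomisation. Neither change balances it, and the write-up should not claim otherwise.

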### Informed Consent and Baseline Assessments

To participate in the study, all participants need to sign an informed consent in the 1st week (Figure 1). Afterwards, irrespective of the group allocation, a semi-structured interview is conducted to assess demographical data: age, gender, employment status, occupation, and marital status. Medical data are evaluated as well: size, bodyweight, blood pressure, current medications, and information about previous alcohol problems and possible depressive episodes. In addition, the questionnaires described below (Table 1) are filled out together with the participants. Lastly, blood samples are collected. This appointment is also used to prepare the test persons for the topics and contents of their respective groups.

**Table 1 T1:** Overview of questionnaires, physiological assessments, and time points.

**Assessment category**	**Assessment instruments**	**First session**	**Last session**	**Between sessions**
Baseline	Demographics	x		
Circadian	Sleep-Food-Diary			x
	Munich ChronoType Questionnaire (MCTQ)	x	x	
	Pittsburgh Sleep Quality Index (PSQI)	x	x	
Alcohol use	Alcohol use disorders identification test (AUDIT)	x	x	
	European Addiction Severity Index (EuropASI)	x	x	
	Timeline Followback 30 (TLFB)	x	x	
Depression	Hamilton Depression Scale (HAMD)	x	x	
	Inventory of Depressive Symptomatology (IDS-SR)	x	x	
Self-efficacy	Self-Efficacy Questionnaire (SWE)	x	x	
Blood values	Blood draws	x	x	

The further course of the study and the contents of the following appointments are described separately for the intervention group and the control group.

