## Study Design

### Design

The study is a 6-weeks trial with a controlled, randomized, single-blinded, parallel-group design including patients with a diagnosis of AUD. Patients are randomly assigned to either an intervention group (DAILY) or a sham control group (placebo treatment). As this study represents a pilot randomized trial, which does not primarily focus on proving treatment successes but more on ascertaining the best options for the future main trial, we will include each eligible patient within this year instead of using formal power calculations (64).

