### Recruitment

In order to facilitate recruitment, a logo was designed for the DAILY study, which has a high recognition value for the test persons and underlines the official character of the study (Figure 2). After screening for eligibility, participants are recruited during their clinical stay at either the specialist ward or the outpatient clinic for addiction disorders. A member of the study staff addresses the candidates personally and finds out whether there is in principle interest in participating in a concomitant therapy study for AUD patients. Candidates are given at least 1 day to consider. In the event of positive feedback, they are allocated to either the intervention or control group.

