Furthermore, at this meeting the test persons are again made aware of the importance of very regular eating and sleeping times. If the test diary shows that the test person has lived rather irregularly, solutions are developed for maintaining more daily regularity. This session also serves as an opportunity to answer potential questions from the study participants and to remind them of the importance of adhering to the daily structure plan that has been drawn up. Participants receive new blank diaries which they are asked to fill in for the next 4 weeks. The times of the designed daily structure plan are handwritten in the empty diary pages as a visual support for precise adherence to the times.

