#### Weeks 3–6: Self-Employed Application of the Daily Structure Plans, Telephone Appointment, and Final Assessment

Starting from this point in the study, the test persons are asked to independently implement the previously developed daily plan for the next 4 weeks and to continue filling out their diaries. The implementation of the daily structure plan can already start at times when the patients are still on the ward or in the day clinic, as patients are allowed to choose the times of all activities (going to bed, eating, leisure activities) freely, with the exception of the fixed therapy sessions on weekdays (see above). However, many patients are discharged or transferred to another institution at different times during this phase of the study. Patients who are discharged home will be asked to follow up the daily schedule outside the clinical setting. Patients who continue their treatment in other institutions will be asked to maintain their daily schedule as much as possible in their new environment. During this time, they can contact the study staff for further assistance (i.e., to adjust the daily structure plan). After 2 weeks, participants are contacted by the study staff by telephone. The telephone call follows the rules of motivational interviewing (65) in order to motivate and remind the participants to further keep to the agreed daily structure and to continue to fill in the diaries thoroughly. If desired, patients are asked to send already completed diaries by fax, mail, or email. The continuous completion of the diary during the application phase of the study serves not only for continuous data collection but also for self-monitoring and increasing compliance. Another 2 weeks later, a last individual appointment is arranged. During this session, diaries will be collected, the questionnaires from the first session are repeated and another blood sample is taken (Table 1).

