Additionally, a questionnaire specially designed for this study with a total of 30 questions and a 4-step ordinal scale for the answers to assess the rating of the participants' subjective structuredness in their everyday life will be filled out. This questionnaire includes, for example, questions on the subjective assessment of whether activities such as eating, sleeping and sport are carried out regularly, whether relapses are associated with irregular daily routines, and whether the craving for alcohol usually occurs at the same time of day. To give the subjects of the control group no indication of the actual aim of the study, the questions that aim at the circadian daily structure are mixed with neutral questions.

Drinking behavior and daily craving will be assessed with questionnaires and the diary, respectively (Table 1). General drinking habits of the last few weeks are surveyed using the AUDIT questionnaire. In addition, the European Addiction Severity Index (EuropASI) is used, which covers not only alcohol and drug consumption but also physical, psychological, financial, and social problem areas of addicted patients. The number of alcoholic drinks and the number of alcohol-free days within the past 30 days is assessed by means of the Timeline Followback 30 (TLFB-30). The diary, which the subjects fill out to collect the Routine Variability Scores, additionally records the highest craving for alcohol on a scale of 0–10 of each day.

According to our secondary hypothesis that the stabilization of circadian rhythms contributes to the reduction of depressive symptoms and increased well-being, changes in the affective state, with a focus on depressive symptoms, are measured with the external assessment questionnaire Hamilton Depression Scale (HAMD) and with the self-reporting questionnaire Inventory of Depressive Symptomatology (IDS-SR). Sleep quantity and quality will be assessed by Pittsburgh Sleep Quality Index (PSQI). Furthermore, for measuring if the DAILY structure program will influence the feeling of self-efficacy, we will employ the Generalized Self-Efficacy Scale (GSES).

As exploratory outcomes, it will be documented how many subjects in the DAILY intervention group and the control groups discontinue the therapy. Furthermore, possible changes of the chronotypes in the course of the study will be defined by the Munich ChronoType Questionnaire (MCTQ).

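### Outcome questionnaires, including the primary drinking measures, are completed jointly with staff who evidently know the arm; the self-report forms could be completed alone at almost no cost

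*Protocol article*

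**What the plan says.** **Blinding.** Under Design the trial is called single-blinded. Allocation makes clear who is meant: until the study ends, "the participants will not be informed about their assignment to the intervention or control group". Of the study code it says: "The decoding of the code is only allowed for study staff".

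**Timing of allocation.** Under Recruitment, candidates get at least a day to consider. "In the event of positive feedback, they are allocated to either the intervention or control group". Allocation therefore comes before the baseline appointment.

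**Mode of assessment.** At baseline, "the questionnaires described below (Table 1) are filled out together with the participants". Table 1 lists MCTQ, PSQI, AUDIT, EuropASI, TLFB, HAMD, IDS-SR and the self-efficacy form. The same paragraph says that this appointment also prepares participants for what their own group will cover. At the last individual appointment the diaries are collected, "the questionnaires from the first session are repeated and another blood sample is taken".

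**What the questionnaires measure.** Measured Outcomes names drinking behavior as a primary outcome and takes it from AUDIT, EuropASI and TLFB-30. Depression is measured with the "external assessment questionnaire Hamilton Depression Scale (HAMD) and with the self-reporting questionnaire Inventory of Depressive Symptomatology (IDS-SR"). Sleep (PSQI) and self-efficacy are secondary.

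**The diary.** In the intervention arm, "The times of the designed daily structure plan are handwritten in the empty diary pages". The control group gets no such plan.

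**The concern.** Single-blinding is meant to keep knowledge of the arm from influencing what is recorded. Here it covers one side of the table only. If the staff member helping to fill in the form knows the arm, blinding the participant does not stop that person's expectations from colouring prompts, clarifications or the recorded answer. Nor does it stop participants from giving the answer they think is wanted.

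This matters most for the drinking measures, because admitting a relapse or low mood face to face is harder than writing it down. DAILY participants are taught that regularity matters for addiction and depression, reminded to keep to their plan, and telephoned to motivate adherence. Controls discuss alcohol in society and advertising. Any such distortion would plausibly be larger in DAILY and run in the direction of the hypothesis. An inflated pilot result would then feed into the main trial that this pilot is meant to prepare.

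Four of the exposed instruments (AUDIT, IDS-SR, PSQI, self-efficacy) do not need a staff member to take part in the answers.

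**Working it through.** The article gives no figure for this bias, so there is nothing of the plan's own to reproduce. The check is mainly a reading of the sections side by side.

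**1. Do the staff at the assessment know the arm?**
- Study staff may decode the study code (Allocation).
- Allocation is done before the baseline appointment (Recruitment).
- The baseline appointment includes arm-specific preparation (Informed Consent and Baseline Assessments).

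Whoever runs that appointment must know the arm to give that preparation. The article does not say so outright, but no other reading fits. At the last session the DAILY diary, with plan times written in, would show the arm to anyone who collects it.

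**2. Are the forms completed jointly at the endpoint?** The statement about joint completion is in the baseline section. For the last session the article says only that the questionnaires are repeated. With no other mode, rater or order given, the natural reading is the same procedure. This is an inference.

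**3. Which outcomes are exposed?**

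| Outcome | Source | Exposed to staff presence? |
|---|---|---|
| Drinking behavior (primary) | AUDIT, TLFB, EuropASI | Yes |
| Depression (secondary) | HAMD, rated by another person | Yes; self-completion is not possible |
| Depression (secondary) | IDS-SR, self-report | Yes; avoidable |
| Sleep, self-efficacy (secondary) | PSQI, self-efficacy form | Yes; avoidable |
| Routine Variability Score (primary) | Diary filled in by the participant | Outside this point |
| CDT, GGT, MCV | Blood sample | Not open to rater or reporting influence |

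**4. Illustration of size.** Both inputs are assumptions.
- *Sample size.* None is stated. Study Population gives 3–5 participants at a time, Design gives 6 weeks per participant and recruitment within a year: 3 × 52/6 = 26 and 5 × 52/6 ≈ 43.
- *Shift.* Reported scores in DAILY move by δ SD in the favourable direction with no true effect; δ = 0.2–0.3, range 0.1–0.5. The document supports no value.
- *Formula.* Two-sample t-test, two-sided 0.05 (the article gives α but not sidedness). Non-centrality = δ√(n₁n₂/N), df = N − 2. The result is the upper-tail probability of the non-central t beyond the critical value.

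For N = 26 (13 + 13): critical t = 2.064, √(169/26) = 2.550. For N = 43 (21 + 22): critical t = 2.020, √(462/43) = 3.278.

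| δ (SD) | N = 26 | N = 43 |
|---|---|---|
| 0 | 2.5% | 2.5% |
| 0.1 | 4.3% | 5.1% |
| 0.2 | 7.1% | 9.4% |
| 0.3 | 11.0% | 15.9% |
| 0.5 | 23.1% | 36.0% |

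Here δ is the whole reporting shift. Part of it is the participant's own expectation after psychoeducation and would remain if the form were completed in private. The table therefore overstates what private completion could remove.

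**The case against.** **The staffing is not stated.** A reader might infer that the person who taught the DAILY sessions also takes the outcome measures. The article does not say this. It speaks of a study assistant for the psychoeducation and of study staff for the telephone call, and names nobody for the last session. This stands, and the point does not rely on it: it needs only that the person present knows the arm.

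**The quoted sentence is about baseline.** This also stands. Endpoint joint completion is inferred, and a full protocol could specify otherwise. But the article does describe the last session and gives no different mode.

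**There are safeguards.** Controls have the same number of sessions and equal staff attention (Control Group), participants are not told their arm, and the study's own structuredness questionnaire hides its circadian items among neutral ones. The wish to report abstinence exists in both arms. This weakens the claim of a difference between arms but does not remove it, because equal attention does not make the content of the coaching equal.

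**It is a pilot.** Design says that proving treatment success is not the main focus, so a false-positive rate is not the central harm. That is fair. Still, the article tests at α < 0.05 and uses the results to choose options for the main trial.

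**Therapists cannot be blinded, and the remedy cannot blind the HAMD rater.** Both are true. The remedy concerns how the self-report forms are collected. Private completion also costs some missing items, which matters in a small study of recently detoxified patients.

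**Conclusion.** The point holds as an avoidable weakness in outcome ascertainment. The article fixes joint completion at baseline, limits blinding to participants, and gives no blinded rater or private mode for the repeat. Questionnaire-based drinking, sleep, depression and self-efficacy scores are therefore open to staff-presence and social-desirability bias, plausibly greater in DAILY.

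This rests on two inferences: that the staff present know the arm (strong) and that the last session uses the same mode as the first (reasonable, not stated).

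The size is unknown. A reader might take the 7–16% as the trial's actual false-positive risk. The documents do not support that, since both the shift and the sample size are assumed and only part of the shift comes from staff presence. A reader might also conclude that single-blinding protects none of the outcomes. That goes too far: the diary-based Routine Variability Score is outside this point and the blood markers are not exposed to it.

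The change is worth making because it is cheap, even though the gain cannot be quantified.

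**What to change.** 1. At the first and last sessions, participants complete AUDIT, IDS-SR, PSQI and the self-efficacy form alone, before any discussion and before diaries are handed in. Forms are returned in an envelope marked with the study code only. Staff answer comprehension questions and check for blank items, nothing more.
2. The TLFB is either self-completed with a calendar or administered by a fixed script before the diaries are opened. Unaided completion is debatable, so choose one way and use it in both arms.
3. State that the HAMD is an unblinded rating and treat it as supportive. Do the same for the EuropASI, assuming staff administer it (the article does not give its mode). Interpret depression mainly from the IDS-SR.
4. Read self-reported drinking alongside CDT, GGT and MCV, which are already collected in both arms at baseline and at six weeks.
5. Add to Limitations that outcome assessment is not blinded on the staff side.

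**Cost.** A change in session order, envelopes and a few lines of text; no extra staff. Expect some more missing items, and a few participants will need help with the forms. Participants' own expectations remain.
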